### Sample Size Estimation

For the longitudinal study (phase 1) a convenient sample of 1216 adolescents will allow detection of a small effect size for regression-based models according to potential predictors (α=.05; power=0.80). After a 25% increase to account for potential dropouts, the estimated final number of participants will be 1520 adolescents.

For the HRV measure, to detect a medium effect size with 80% of power [55], at least 61 healthy adolescents need to be recruited. For the analysis of the genotyping serotonin transporter polymorphisms 5-HT1AR and 5-HT2AR, based on the effect sizes reported in Matsunaga et al [47], an a priori power analysis estimated that 191 participants would be necessary to detect a small-to-medium effect size (α=.05; power=0.80).

For phase 2, applying the criteria of data saturation, around 12 FGs distributed across schools in Italy are expected to be sufficient to explore all the relevant topics. The final number will be adjusted according to the data saturation criteria. As for the co-design workshops, a purposive sample of around 20 midadolescents is evaluated sufficient.

For phase 3, all the adolescents who took part in phase 1 of the project will be invited to participate in this phase. Considering that longitudinal studies on unguided self-help interventions report up to 63% of drop-out rates [56] and that this phase will start after several months from the first recruitment, we expect a final sample of around 400 adolescents participating in this phase, which is considered sufficient for feasibility and pilot aims.

### Intervention

The SMART app will aim to promote awareness and functional SM use. The app will use unguided web-based self-help approaches, that is a self-help program that does not include any contact with a therapist or researcher during its use, although it may include automatic reminders through app notifications (eg, to motivate the app use, or to complete an app session).

The app will be created according to the co-design described above and contents based on the more recent literature in the field, considering the evidence-based interventions already developed for PSMU and the empirical data derived from quantitative and qualitative data collected during the current project. To date, to the best of our knowledge, among the most widely used approach we have cognitive behavioral therapy, psychoeducational, positive psychology, and multifamily group therapy ones [57]. Among the preexisting theoretical models of PSMU, the systemic and cognitive-behavioral psychological models emerged. Specifically, the compensatory internet use theory [7] posits that PSMU could be conceptualized as a maladaptive coping mechanism that allows individuals to manage their negative emotions, to escape from disturbing issues and to regulate negative moods.

Although all the contents will be adapted according to the collected results and co-design, ideally the core features of the app will prioritize strategies aimed at improving emotional awareness, emotions regulation and interpersonal skills, specifically in relation to the context of SM use. Based on both theoretical and clinical knowledge and experience in the field, the app will ideally include several interactive modules, including: (1) an informative and awareness section with different educational contents (eg, information regarding SM use, consequences of PSMU, and SM role in defining individuals’ identity); and (2) a psychoeducational section aimed at promoting emotional awareness and skills and adolescents’ personal and interpersonal resources in order to prevent PSMU and promote functional SM use (eg, how to manage the pervasive apprehension that others might be experiencing rewarding activities that one could miss out; how to change negative thinking patterns; problem-solving strategies). Videos, practical scenarios, and examples (collected during FGs or co-created with adolescents during workshops) will be potentially used to promote engagement. The tone and contents of messages will be adapted according to the feedback from adolescents to ensure informative, nonjudgmental, and supportive communication as well as to motivate adolescents to use the app. Moreover, the app developers will use some specific tools to foster the readability and comprehensibility of the app (including, for example, the Simple Measure of Gobbledygook Index, Hemingway app).

### Ethical Considerations

In compliance with the ethical standards for research outlined in the Ethical Principles of Psychologists and Code of Conduct [58], approval by the Ethics’ Committee have been required and obtained by the Ethical Committee of the Umbria Region (protocol 4637/23). In order to participate in the study, written consent from parents or legal guardians and oral assent from midadolescents will be obtained. The informed consent will inform parents or legal guardians and midadolescents around the purposes of the research, the expected duration, the procedures, the absence of potential risks including physical, mental, and social injury, and participants’ right to withdraw at any time from the study if not willing to continue. Participation will be voluntary, and no monetary incentive will be given. In all the different phases of the study, data will be collected to assure participant’s privacy and confidentiality protection (eg, pseudonymization during the data collection and anonymization during the dissemination phase). All research teams will also protect the values, rights, and interests of the participants and respect basic ethical principles such as nonmaleficence, informed consent, and fair treatment. All data will be collected according to the EU General Data Protection Regulation.

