## Introduction

### Background

According to the World Health Organization, one-sixth of the global population is composed of adolescents, and this number is expected to rise through 2050 [1]. Unfortunately, 1 in 7 adolescents experience mental health conditions, which remain largely unrecognized and untreated. Also, given the widespread use and pervasiveness of new technologies among adolescents, it is not surprising that 60.43% of Italian adolescents report an intense or a problematic social media (SM) use (PSMU) [2] and, although to our knowledge, no estimations regarding the direct or indirect financial cost or societal burden of PSMU are currently available, it has been hypothesized that PSMU may have relevant costs both for individuals (eg, mental and physical health, social functioning) and societies (eg, direct health care costs and indirect costs following productivity losses).

SM is made up of various digital user-driven platforms (eg, Facebook, TikTok, Instagram) that facilitate connectivity and engagement between individuals as well as allow to create and share user-generated content [3]. PSMU is considered an etiologically complex behavior associated with psychological distress, although this relation is far from being completely understood [4] and the conceptualization of PSMU is still debated. To date, the absence of a commonly accepted definition could be linked to the rapidly changing nature of SM as well as to the inconsistent results obtained by prior research on PSMU among adolescents [5]. Technology and SM are an integral part of the daily life of today’s teenagers, who use them to create a virtual space to satisfy their needs for communication, social contact, belonging, comparison, and self-realization. However, some scholars defined PSMU as an “addictive-like” behavior (eg, associated with salience, tolerance, withdrawal, and relapse) [6], hierarchically arranged (ie, with different levels of excessive or disordered use) and whose main characteristic is a lack of self-regulation in one’s own SM use [4].

Nonetheless, the adoption of an addiction paradigm to describe PSMU has been criticized [7].

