### Participant Recruitment and Setting

The target group (adolescents aged 14-18 years) will be actively involved in the various actions of each phase. Participants will be recruited from schools (ie, secondary school), in the north, central, and south Italy. Each research team will select schools (on a voluntary basis or following previous collaborations) and interact with stakeholders (regional and local school offices, school communities) to obtain their availability for participation. Attention will be given to contacting schools located in particularly disadvantaged areas and to include students with different sociodemographic and cultural backgrounds and levels of vulnerability. At each participating school, adolescents may participate in the different phases of the study.

The following inclusion criteria will be followed for participation in each included school: (1) having an age between 14 and 18 years, (2) having signed the consent form for the study participation (ie, consent to participate for adolescents less than 18 years signed by both parents—or legal representatives—or by the adolescent when 18 years); having sufficient knowledge of the Italian language.

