### Procedure and Measures

#### Longitudinal 3-Waves Evaluation (Phase 1)

The longitudinal evaluation study (phase 1) will be articulated across 3-time points of assessment: baseline (T0: around months 3-5), at around 5 months (T1: months 8-10), and at around 10 months follow-up (T2: month 13-15). At each time point, a survey composed by a battery of self-reported questionnaires will be delivered through a dedicated web-based platform during regular school hours.

Diverse theoretical models of PSMU are operationalized in those battery of questionnaires (see Table 2 and Multimedia Appendix 1 for a detailed description of measures and questionnaires) to explore potential intra- and interpersonal psychosocial risk or protective factors of PSMU.

**Table 2 table2:** Self-report questionnaires adopted in the SMART project^a^.

Role of the dimension in the longitudinal study ad questionnaire name			Investigated dimension		Questionnaire’s characteristics		Time

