**Secondary outcomes**							
	Social Emotional Distress Scale—Secondary [43]	Emotional distress		10 Items, 4-point Likert scale		T0, T1, T2, and T3	
	Passive Social Networking Site Use Questionnaire [44]	Passive SM use		5 Items, 5-points Likert scale		T0, T1, T2, and T3	

^a^Time: time of administration; T0 (baseline) corresponds to months 3-5, T1 to months 8-10, and T2 to months 13-15. T3 is an additional time point (at the end of the app intervention) explained in phase 3.

^b^SM: social media.

Moreover, in a subsample of participants, momentary emotions or feelings (eg, happy, sad, tired, relaxed, nervous, quiet, each rated on a visual analogue scale) as well as the subjective use of SM during the past 2 hours will be recorded at 1 time point through an ad hoc app, using an ecological momentary assessment approach [45]. Momentary questions will be randomly delivered during nonschool hours (ie, from 3 to 10 PM), for a total of 4 times per day, for 2 weeks.

At baseline, 2 additional biological markers of PSMU will be randomly collected in vivo in a subsample of participants. First, the autonomic activity of the participants will be collected with the aim of testing whether a greater PMSU is associated with a decreased vagal (ie, parasympathetic) activity at rest. This autonomic parasympathetic activity—considered a physiological index of emotion dysregulation [24]—will be investigated through specific indices of heart rate variability (HRV) such as the high frequencies and the root mean square of successive differences between normal heartbeats [46]. The HRV will be continuously recorded during 10-minute resting condition using a wearable electrocardiogram device. The second biomarker is the presence of specific polymorphisms for serotonin gene transporter 5-HT1AR and 5-HT2AR that—according to the bipartite model of brain serotonin functions [25]—seem to be associated with a greater risk of developing internalizing disorders [47], such as PSMU. The presence of these polymorphisms will be tested through saliva samples, collected with a saliva stick and processed by the University of Perugia.

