#### Qualitative Focus Group Study and Co-Design Approach (Phase 2)

Focus groups (FGs) have been widely used as a method for exploring people’s perspectives and experiences by using the group interaction to encourage the participants to explain, disagree, and share their views [48]. This method is particularly useful in research with adolescents [49]. Through FGs, we will explore the adolescents’ point of view regarding the following topics: the adolescents’ perspectives regarding the main purposes and modalities of SM use; the link between SM use, psychological distress, and well-being; risk factors associated with PSMU and protective strategies and resources that may be activated to promote functional use of SM. Each FG will be led by a moderator and an assistant (both with expertise in conducting FGs and in clinical psychology) and will last around 90-120 minutes each. Each FG will include around 8 to 10 adolescents, recruited through purposive sampling in the participating schools and balanced for sociodemographic variables, according to the suggestions of Palinkas et al [50], and the availability of the participating schools.

FGs will be conducted following a shared interview guide, including a set of open-ended questions and following a semistructured approach. While conducting the FGs, researchers will also pay attention to the group dynamics, ensuring that a good atmosphere is maintained. Before the FG, participants will fill out a brief questionnaire to collect background information (eg, sociodemographic information, emotional distress, and SM use) to describe the sample.

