In terms of impact, the project investigates a stage of life that has been strongly affected by the pandemic of COVID-19 [75]. The latter negatively impacted midadolescents’ need for autonomy and social interaction, causing anger and loneliness that some of them self-regulated through an increased use of SM. Therefore, the SMART project results may help better understand an actual adolescents’ need, worsened by the COVID-19 pandemic’s mental health burden. The SMART project invites adolescents to critically discuss SM use habits and needs and encourages them to share (eg, during FGs or co-design workshops) difficulties that adolescents might present as connected to SM use as well as the potential coping strategies adopted to face them. Even if this is not the aim of the FG, this may indirectly lead to a potential psychological benefit for adolescents in terms of normalization of the experience and reduction of isolation. The participatory approach actively engages adolescents to fully participate in designing an age- and culturally appropriate app-based self-help intervention. Empowering youths to play an active role in their well-being is one of the key foci of the participatory approach in promoting healthy communities [76].

Within the project, we will develop and evaluate an unguided self-help app, thus contributing to the advancement of knowledge on eHealth interventions for SM use and PSMU in adolescence. This simple and easy-to-use app, including interactive and supportive contents, will be based on adolescents’ preferences and inputs and on evidence-based intervention models, and will: (1) promote a healthier use of SM among midadolescents; (2) help them to become more aware of a potential PSMU; (3) mitigate the impact of psychosocial and biological risk factors on PSMU; and (4) boost their confidence through the use of more adaptive coping strategies while facing stressful events. The results from the pilot study may guide future multinational RCT studies for the evaluation of app effectiveness. Finally, in future research, the self-help app may be adapted to the special needs of adolescents with different PSMU profiles.

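### The consent content described in the article denies any potential physical, mental or social risk, which conflicts with the study procedures described in the same article

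*Protocol article*

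**What the plan says.** The Ethical Considerations section lists what the informed consent will convey to parents or legal guardians and to adolescents. Next to purpose, duration, procedures and the right to withdraw, it lists "the absence of potential risks including physical, mental, and social injury".

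Other sections describe what participants will be asked to do:

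- **Surveys (Longitudinal 3-Waves Evaluation, Phase 1).** "At each time point, a survey composed by a battery of self-reported questionnaires will be delivered". Table 2 schedules the emotional distress scale, a secondary outcome, at T0, T1, T2 and T3.
- **Momentary assessment (text following Table 2).** A subsample rates momentary feelings, both pleasant and unpleasant, "for a total of 4 times per day, for 2 weeks".
- **Genotyping (same place).** A subsample gives saliva at baseline to test for serotonin-related polymorphisms, which the article links to a greater risk of internalizing disorders.
- **Focus groups (Phase 2 section and Statistical Analyses).** About 12 groups of 8 to 10 adolescents, recruited in the participating schools, are audio-recorded and transcribed. The Expected Findings section says the project "encourages them to share (eg, during FGs or co-design workshops) difficulties that adolescents might present as connected to SM use".
- **Use of focus group material (Intervention and Statistical Analyses).** Scenarios and real-life examples gathered in the groups may be used in the app. The phase 3 section says the app is offered to all recruited adolescents.

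**The concern.** The wording denies even potential risk, and it names mental and social injury among the risks denied. The study asks minors about distress repeatedly, brings them together to talk about their difficulties in front of peers, records them, and takes genetic material from some. Each of these has a foreseeable, if probably modest, mental, social or privacy risk.

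The issue is the basis on which families decide. If the consent follows the description, parents and adolescents weigh participation on a statement that the plan does not support. A participant who is upset by a question, or regrets something said in a group, will have been told that this could not arise from taking part. The point concerns something the article states, not a detail it leaves out, so the brevity of a journal article does not explain it.

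**Working it through.** No sample-size, power or error-rate figure enters this point, and the plan states no figure to reproduce. The check sets the risk statement beside each procedure and counts the exposures.

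**Counts from the article**

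- Distress scale: T0, T1, T2 and T3 = 4 administrations for those who go on to phase 3, and 3 for those in phase 1 only.
- Momentary prompts: 4 per day × 14 days = 56 per participant in that subsample.
- Focus group members: 12 × 8 = 96 to 12 × 10 = 120. The number of groups is approximate and may change with data saturation.

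**Risk statement against procedure**

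1. *No mental risk.* Participants answer a distress scale at every wave, and some also rate current feelings, including sadness and nervousness, up to 56 times. Some upset from such questions is foreseeable. The Expected Findings section also says that sharing in the groups may indirectly bring psychological benefit. An activity accepted as able to change an adolescent's psychological state for the better cannot, without argument, be described as unable to change it for the worse.
2. *No social risk.* In each group, 7 to 9 other adolescents (8 − 1 to 10 − 1) hear what a participant says. The article gives pseudonymization as an example of its privacy protection. That protects the research record; it does not govern what peers hear or repeat. Examples from the groups may then appear in an app offered to the whole cohort, and a vivid example could be recognised by someone who was present.
3. *No potential risk at all.* Genetic data from minors raise a question of data handling that the unqualified wording leaves no room for.

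**Timing**

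The Results section reports that T0, T1 and the focus groups were complete by July 2024. T2 and phase 3 were still ahead, and the co-design workshops were not reported as complete. Saliva was planned at baseline, so sampling has presumably taken place and the remaining issue is how those data are handled. The article does not say at which wave momentary assessment takes place.

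**The case against.** The strongest reply is that the consent form is not shown: one clause in an article summarises it, and the form may name risks properly. Ethics approval was obtained. The article also states voluntary participation, the right to withdraw, nonmaleficence and compliance with data protection law. Both focus group leaders have clinical psychology expertise and attend to group dynamics. The momentary items include pleasant as well as unpleasant feelings. The exposure counts estimate no harm, and the focus groups are already done.

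Much of this stands as mitigation and limits how much weight the point can carry. It does not remove the conflict. Approval does not make the described wording consistent with the described procedures, and safeguards reduce a risk without showing that none exists. If the form does name risks, the article misreports it and still needs correcting.

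A reader might infer more than the documents support:

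- **That nobody is assigned to act on distress scores.** The article is silent on this. Such arrangements commonly sit in the full protocol or ethics file, which are not shown, and clinical psychologists conduct the project. The phrase "eg, sociodemographic information, emotional distress, and SM use) to describe the sample" concerns only the short questionnaire before the focus groups and says nothing about how the wave surveys are handled.
- **That the sample is selected for vulnerability.** The recruitment section gives attention to schools in disadvantaged areas and aims "to include students with different sociodemographic and cultural backgrounds and levels of vulnerability". That is diversity within voluntary school recruitment.
- **That disclosure takes place in front of schoolmates.** Groups are recruited in the participating schools, but the article does not say that each group comes from a single school.
- **That the prevalence quoted in the Background measures the problem.** The statement that "1 in 7 adolescents experience mental health conditions, which remain largely unrecognized and untreated" concerns existing conditions in the population. It does not measure harm from taking part, so no count of affected participants is derived from it here.

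**Conclusion.** The point holds in a limited form. The consent content described in Ethical Considerations, that no potential physical, mental or social risk exists, is contradicted by procedures described elsewhere in the article, and the passages must be reconciled.

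Its size can be given only as exposure: up to 4 distress assessments per participant, up to 56 momentary prompts in one subsample, saliva genotyping in a subsample, and about 96 to 120 focus group members. The documents do not allow any estimate of how often harm would occur, and the risks may well be small. A small risk is still not an absent one.

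The conclusion assumes that the article reports the consent content faithfully. It should not be read as a finding that families were in fact misinformed, because the form has not been seen. Whether and how distress scores are reviewed during the study is a question for the investigators and the ethics committee; no fault is claimed there.

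**What to change.** Reconcile the risk statement in Ethical Considerations with the text following Table 2, the Phase 2 section, Intervention, Statistical Analyses and Expected Findings:

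1. Check the article's clause against the approved consent form. If the form already names risks, correct the article.
2. If the form does carry the denial, remove it and name the foreseeable risks: upset from distress and mood questions, disclosure to peers in group sessions (including recognition of examples reused in the app), and handling of genetic data.
3. Give families the corrected information before the steps still to come: T2, any remaining workshops, and phase 3. For focus groups already held, the correction cannot inform the decision to join, but it can inform the use of the material collected.

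The cost is revised wording and an ethics amendment. Naming risks may lower participation slightly. No outcome, visit or analysis needs to change.

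Separately, and as a question only: does the ethics file set out whether and how distress scores are reviewed during the study?
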